**Table 9. Relationship between adverse events and the investigational vaccine**

|                             |                                                                                                                                                                                                                                                                      |
|-----------------------------|----------------------------------------------------------------------------------------------------------------------------------------------------------------------------------------------------------------------------------------------------------------------|
| Definitely Unrelated | The symptoms differ from the expected post-vaccination reactions or are not temporally related to the vaccination. The symptoms may be caused by other diseases or treatments, and they resolve or disappear after the disease improves or the treatment is stopped. |
| Possibly Unrelated   | The symptoms differ from the expected post-vaccination reactions or are not temporally related to the vaccination. The symptoms may be caused by other diseases or treatments.                                                                                       |
| Possibly Related     | The symptoms are similar to the expected post-vaccination reactions and/or align with the expected timing of post-vaccination reactions. The symptoms resolve or improve after vaccination is stopped and cannot be explained by other causes.                       |
| Definitely Related   | The symptoms and their timing are consistent with the expected post-vaccination reactions. The symptoms resolve or improve after vaccination is stopped and reappear upon re-vaccination.                                                                            |
| Unable to Determine  | The symptoms may be caused by factors outside the trial but are similar to post-vaccination reactions and/or their timing may be related to vaccination. It cannot be ruled out that the symptoms are adverse events caused by the vaccine.                          |

The grading of adverse events will be determined after review by the head of the clinical trial unit. The relationship between adverse events and vaccination will be preliminarily assessed by the researchers at the clinical trial unit, but the final determination will be made through discussion between the sponsor and the clinical trial unit and confirmed in writing.

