#### **6.2.1 Primary Endpoint Events**

##### **6.2.1.1 Primary Safety Endpoint Event**

During the clinical trial, the safety indicators are graded according to Annex 2, and the following are the primary safety endpoint events:

- (1) Grade 3 or higher local adverse reactions;
- (2) Grade 3 or higher systemic adverse reactions;
- (3) Any events of immunization regimen termination caused by vaccine problems;
- (4) Any event leading to the discontinuation of the immunization schedule due to vaccine-related issues.

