### 6.5.6 Evaluation of the Relationship between Adverse Events and the Investigational Vaccine

Adverse Events (AEs) refer to any unfavorable or unintended experiences that occur in participants during the clinical trial. Serious Adverse Events (SAEs) are those that result in any of the following outcomes:

1. Death;
2. Life-threatening conditions;
3. Hospitalization or prolongation of existing hospitalization (excluding hospitalization due to pre-existing conditions);
4. Persistent or significant disability or incapacity;
5. Congenital anomalies or birth defects (in cases where the participant is pregnant);
6. Other significant medical events (e.g., allergic reactions requiring emergency treatment, seizures not requiring hospitalization or medication, etc.).

Based on the criteria in Appendix 2, participants' systemic and local adverse events, as well as laboratory test abnormalities, will be graded. Social harm should also be classified as an adverse event.

According to their relationship to the investigational product, adverse events can be categorized into one of the following:

1. Definitely unrelated to vaccination;
2. Possibly unrelated to vaccination;
3. Possibly related to vaccination;
4. Definitely related to vaccination;
5. Unable to determine the relationship.

The latter three categories are considered adverse events potentially caused by vaccination and are classified as vaccination-related adverse events. Specific criteria for determining the relationship between adverse events and the investigational vaccine are provided in Table 9.

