## Annex 6. Reactions after Smallpox Vaccination and Principles of Treatment

*As this is the first clinical study of rTV vaccine with Tiantan strain of vaccinia virus as a vector, the vaccination reactions caused by the vaccine can be determined only after completion of this clinical trial, and the reactions caused by Tiantan strain of vaccinia virus for smallpox vaccination can be regarded as a reference for expected adverse reactions. However, when constructing the rTV vaccine, the insertion of HIV genes has significantly reduced the virulence of Tiantan strain of vaccinia virus. The experiments of animals have also shown that the toxicity of rTV vaccine in mice is 100-1000 times lower than that of Tiantan vaccinia virus, therefore, the adverse reactions caused by AIDS vaccine should be much lower than those caused by Tiantan strain smallpox vaccine.*

Reactions in human body after smallpox vaccination include general reaction and abnormal reactions. The general reactions are typical local reactions of smallpox and possibly some systemic symptoms after vaccination. An abnormal reaction refers to a rarely serious adverse reaction after vaccination. Tiantan strain vaccinia virus as a smallpox vaccine has been universally vaccinated in Chinese population, and it has played a good role in the prevention of smallpox epidemic, and successfully eradicates smallpox disease in China. Different from the crude smallpox vaccine from tissues such as cow skin used in other countries, Tiantan strain smallpox vaccine is a refined vaccine obtained by cell culture, therefore, it has lower rate of abnormal reactions after vaccination than other smallpox vaccines, with the incidence of approximately 5.6/million for post-vaccination encephalitis, progressive pox, chicken pox rash, generalized pox and pleomorphic smallpox, and 80% of these reactions occur in infants under 1 year of age and immunocompromised persons. There is no report of deaths after vaccination of cell-cultured Tiantan strain smallpox vaccine manufactured by Beijing Institute of Biological Products Co., Ltd. The general reactions and abnormal reactions developed after smallpox vaccination as well as treatment principles are listed by referring to Compilation of Data from Experience Exchange Meeting on Vaccinia in 1974 [35] in China and the data from U.S. CDC on the New York strain smallpox vaccination [36].

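### Table 9's causality classes overlap and leave gaps, so the vaccine-related split behind the grade 3+ reaction endpoint and the halting count is not reproducible and can undercount

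*Protocol*

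**What the plan says.** Protocol Section 6.5.6 sorts adverse events into five causality classes. "The latter three categories are considered adverse events potentially caused by vaccination", and Section 6.10.5 (3) uses the same three (definitely related, possibly related, indeterminable) to define an adverse reaction. Table 9 gives the criteria:

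- *Definitely Unrelated* and *Possibly Unrelated* both start with "The symptoms differ from the expected post-vaccination reactions or are not temporally related to the vaccination" and continue "The symptoms may be caused by other diseases or treatments". *Definitely Unrelated* also expects the symptoms to clear once that other disease or treatment is dealt with.
- *Possibly Related*: "The symptoms are similar to the expected post-vaccination reactions and/or align with the expected timing of post-vaccination reactions". The symptoms must also resolve or improve once vaccination stops and have no other explanation.
- *Definitely Related*: symptoms and timing both match what is expected, and "The symptoms resolve or improve after vaccination is stopped and reappear upon re-vaccination".
- *Unable to Determine*: a factor outside the trial may be the cause, but the symptoms are "similar to post-vaccination reactions and/or their timing may be related to vaccination", and the vaccine cannot be excluded. Improvement is not required.

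The split has two main uses. Section 6.2.1.1 lists "Grade 3 or higher systemic adverse reactions", and the local equivalent, as primary safety endpoint events. Sections 6.4.2 and 6.7.2 halt vaccination on a count of three vaccine-related grade 3+ events, and Section 6.4.2 names Table 9 as the source of the criteria. The text after Table 9 leaves the final causality call to a discussion between the sponsor and the clinical unit, confirmed in writing.

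**The concern.** A causality scale that feeds an endpoint and a halting count should place each event in one class, or at least on one side of the related/unrelated line. Table 9 does not do so for two kinds of event that matter in a first human trial of this combined regimen.

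The first is the event that has not improved and has no other explanation. Both rows that attribute an event to the vaccine require improvement, and the remaining related row presupposes a possible outside cause. Yet Annex 2 uses failure to heal to define some severe grades. A DNA-site blister or ulcer is grade 3 if still unhealed beyond two weeks. A large DNA-site pustule is grade 3 if it shows no sign of healing by two weeks. An rTV pustule is grade 4 if it is still enlarging and unscabbed after two weeks. Low-dose safety is assessed within two weeks of each DNA dose (Section 6.4.2), when an event may still be ongoing.

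The second is the unexpected but timely event for which someone can think of another cause. It meets an uncounted class and a counted class at once.

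With a threshold of three, one event filed as unrelated or left without a class turns a count of three into two.

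**Working it through.** The protocol gives no figure on this point, so there is none to reproduce. The check reads each row of Table 9 literally against four yes/no attributes: symptoms as expected (E), timing fits (T), another cause possible, and resolved or improved. That gives 2^4 = 16 combinations. Recurrence on re-vaccination is left out; it only adds *Definitely Related*, and only to events that already meet a related row.

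DU = *Definitely Unrelated*, PU = *Possibly Unrelated*, PR = *Possibly Related*, UD = *Unable to Determine*.

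| Other cause possible | Improved | E and T | E, not T | T, not E | Neither |
|---|---|---|---|---|---|
| Yes | Yes | UD | DU, PU, UD | DU, PU, UD | DU, PU |
| Yes | No | UD | PU, UD | PU, UD | PU |
| No | Yes | PR | PR | PR | none |
| No | No | none | none | none | none |

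- On both sides of the line: 4 of 16. Exactly one of expectedness and timing is met, and another cause is possible. The *or* in the unrelated rows and the *and/or* in *Unable to Determine* produce this.
- In no class: 5 of 16. Four are the unimproved events with no other cause, including the fully expected and timely one. The fifth is an improved event that is neither expected nor timely and has no other cause.
- Clearly on one side: 16 − 4 − 5 = 7.

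These are counts of logical cases, not of expected events.

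The improvement clause is also circular. It refers to what happens after vaccination stops, but under Section 6.5.8 a related grade 3+ event is what stops a participant's vaccination.

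For scale only, under assumed inputs:

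1. Suppose three grade 3+ events are truly related and each independently has probability q of being filed as unrelated. The count still reaches three with probability (1 − q)^3: 0.9^3 = 0.729 at q = 0.1, 0.7^3 = 0.343 at q = 0.3, 0.5^3 = 0.125 at q = 0.5.
2. Take the 12 low-dose participants, a rate p of truly related grade 3+ events (at most one each), and a share m not counted. The count X is Binomial(12, p(1 − m)). For p = 0.20 and m = 0, P(X ≥ 3) = 1 − (0.0687 + 0.2062 + 0.2835) = 0.442. The full set is:

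| p | m = 0 | m = 0.25 | m = 0.50 |
|---|---|---|---|
| 0.10 | 0.111 | 0.056 | 0.020 |
| 0.20 | 0.442 | 0.264 | 0.111 |
| 0.30 | 0.747 | 0.528 | 0.264 |

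Neither q, p nor m comes from the protocol. The figures show how sensitive a threshold of three is to a few classification decisions, not how often they would go wrong.

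**The case against.** Several stronger readings are tempting, and the protocol does not support them.

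- A reader might infer that Table 9 sends unexpected but timely events to an unrelated class. It permits this but does not force it. *Possibly Related* accepts timing alone, so such an event with no other cause that improves fits only a related class. With another possible cause it also fits *Unable to Determine*, which counts.
- A reader might infer that the rechallenge condition lowers the count, since rTV is planned as one dose. It does not: an event that misses *Definitely Related* only for lack of recurrence can still be *Possibly Related*, and the three classes are pooled. The class is not wholly out of reach either. DNA is given three times, and Section 6.4.3 repeats rTV after an unsuccessful take.
- A reader might infer that expected reactions are undefined, because Annex 6 says "the vaccination reactions caused by the vaccine can be determined only after completion of this clinical trial". The same sentence takes reactions to the Tiantan smallpox vaccine as the reference, and Annex 6 then describes them.
- Not every unresolved event is lost. One that improves but leaves sequelae still qualifies, and one with a possible outside cause has at least one class.

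Oversight does not rest on Table 9 alone. Serious events are reported within 24 hours whatever their causality (Section 6.5.7), and an independent DSMB guides their attribution (Section 7.3.1). The primary safety endpoints in Table 3 count all grade 3+ adverse events and do not use causality.

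All of this stands and narrows the point. It does not supply a class for the unimproved, unexplained event, or a tie-break for the overlap. The sponsor–site discussion names who decides, not by what rule.

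**Conclusion.** The point holds as a fault in a stated rule. Read literally, Table 9 leaves 5 of 16 attribute combinations without a class and puts 4 on both sides of the line. Two competent assessors could therefore reach different counts for the Section 6.2.1.1 endpoint and the halting rule from the same events. The most serious gap is the timely, unexplained event that has not improved, because Annex 2 ties some grade 3 and 4 reactions to failure to heal.

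That the count would be biased low is a risk, not a demonstrated result. The direction depends on how gaps and overlaps are settled in practice, and the wording of *Unable to Determine* pushes towards counting. The probabilities above rest entirely on assumed q, p and m. Separately, Section 6.2.1.1 names adverse reactions while Table 3 names adverse events of any cause. Only the former depends on Table 9, and the two passages need to be reconciled.

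**What to change.** In Table 9:

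1. In *Possibly Related* and *Definitely Related*, change resolution or improvement after stopping from a required condition to supportive evidence. This closes 3 of the 5 gaps: the unimproved events with no other cause that are expected, timely or both.
2. Add one sentence: an event that meets no row, or that meets both an unrelated row and *Unable to Determine* without an identified alternative cause, is classed *Unable to Determine* and counted as vaccination-related. This closes the other 2 gaps and settles the 4 overlaps; an overlap with an identified alternative cause stays in the unrelated row.

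Replacing *or* by *and* in the unrelated rows is not advised. It would remove the overlaps, but it would also bar plainly unrelated timely events, such as an accidental injury on day 2, from those rows.

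Recurrence on re-vaccination may also be made supportive, but this changes only the label within the pooled classes. State in Sections 4 (Table 3) and 6.2.1.1 whether the primary safety endpoint counts events or reactions.

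The cost is a wording change to one table and the matching CRF guidance, made before any event is adjudicated. Somewhat more events will count as related, so the reported reaction rate may look less favourable and the existing halting count may be reached sooner. No dose, threshold or stopping rule is altered.

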dose subgroup. Enrollment and vaccination will begin with the low-dose subgroup of the combined immunization group in the order of enrollment. The safety of the vaccine will be assessed within two weeks after each DNA vaccination in the low-dose subgroup. If no more than two vaccine-related adverse events of grade  $\geq 3$  (excluding fever above 39°C for no more than 3 days) occur, the trial will continue; if three or more such adverse events occur, subsequent vaccinations will be halted. Participants in both dose subgroups of the combined immunization group and the DNA-only group will receive three doses of 2 mg (low-dose subgroup) or 4 mg (high-dose subgroup) of the DNA vaccine at 4-week intervals. Enrollment and vaccination for the DNA-only group will commence simultaneously with the high-dose subgroup of the combined immunization group. If no more than two vaccine-related adverse events of grade  $\geq 3$  occur after each 4 mg DNA vaccination in the high-dose subgroup and the DNA-only group, the trial will continue; if three or more such adverse events occur, subsequent vaccinations in that dose subgroup will be stopped. If no more than two vaccine-related adverse events of grade  $\geq 3$  occur after the third DNA vaccination in each group, the combined immunization group will receive the rTV vaccine at the dose determined by the Phase Ia trial four weeks after the last DNA vaccination, while the DNA-only group will receive a placebo of the corresponding dose of the rTV vaccine. The placebo group will begin enrollment and vaccination at the same time as the low-dose subgroup of the combined immunization group and will receive placebos of the same volume as the DNA or rTV vaccines at the same time points. After the last vaccine or placebo administration, all participants will undergo at least six consecutive months of clinical and laboratory observation. In the Phase Ib trial, the interval between vaccinations in each group will be  $\geq 4$  weeks; if the time required for adverse reactions to heal or resolve exceeds 4 weeks, the interval between vaccinations will be  $\geq$  the actual time required for healing. The criteria for determining adverse events and their relationship to vaccination are detailed in Appendix 2 and Table 9.

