## 6.7.2 Early Termination of the Clinical Study

In the low-dose combined immunization group, if three or more vaccine-related adverse events of grade  $\geq 3$  (excluding fever above 39°C for no more than 3 days) occur after each vaccination, the sponsor and the clinical trial unit should terminate subsequent vaccinations for all groups. However, follow-up for the affected participants should continue at least until the adverse events are resolved.

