### **7.3.1 Data and Safety Monitoring Board**

A Data Safety Monitoring Board (DSMB), composed of renowned domestic statisticians, clinical experts, vaccinologists, and ethicists independent of the study sponsor and clinical trial investigators, will be established. The DSMB is tasked with reviewing the study protocol, overseeing the execution of the clinical protocol, regularly reviewing data safety reports, and auditing the phases and final summary of the clinical trial. This is to safeguard the interests of the subjects and ensure the scientific integrity and completion of the clinical research. The DSMB will convene every two months to discuss research data reports submitted by the data center, guide the sponsor and clinical trial units in determining the relationship between serious adverse events and the study vaccine, and provide recommendations to the sponsor for modifying the clinical protocol or terminating the study. Following each meeting, the DSMB will submit written opinions and recommendations to the sponsor.

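### The joint sponsor–site causality decision can replace the site's own assessment in the halting count, with no rule for disagreement, and at exactly three events one recategorisation turns a halt into a continue

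*Protocol*

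**What the plan says.** **Who decides.** The paragraph after Table 9 in Protocol section 6.5.6 separates severity from causality. On severity: "The grading of adverse events will be determined after review by the head of the clinical trial unit". On causality, the site's researchers give only a first, provisional view. The binding one is settled afterwards: "the final determination will be made through discussion between the sponsor and the clinical trial unit and confirmed in writing". Section 5.1 names two sponsors, and the Synopsis describes them as joint developers of the vaccine.

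**What counts as related.** Section 6.5.6 has five categories. Possibly related, definitely related and unable to determine all count as vaccination-related. Possibly unrelated and definitely unrelated do not.

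**What the label drives.** Section 6.4.2 reviews low-dose safety within two weeks of each DNA dose and counts only vaccine-related events of grade 3 or higher, leaving out short-lived fever above 39°C. Up to two events means continue; "if three or more such adverse events occur, subsequent vaccinations will be halted". For the 4 mg groups, "if three or more such adverse events occur, subsequent vaccinations in that dose subgroup will be stopped". Section 6.7.2 repeats the low-dose rule for each vaccination and says that "the sponsor and the clinical trial unit should terminate subsequent vaccinations for all groups". Sections 6.5.8 and 6.7.1 also use relatedness for one of the grounds on which an individual's vaccination is discontinued.

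**Independent input.** Under section 7.3.1 the Data Safety Monitoring Board guides sponsor and site on the causality of serious adverse events, reviews data safety reports and may recommend termination. "The DSMB will convene every two months".

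**The concern.** The halting rule is a small-count rule: two events or fewer means continue, three or more means halt. A rule of this kind is only as robust as the label that admits an event to the count. Here the site's label is provisional and the binding one comes from a discussion that includes the sponsors. In the low-dose group the same two parties then act on the count.

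The protocol has no default. It does not say which view stands if the parties differ, whether the more cautious view prevails, or whether the site's first assessment stays on record for the count. In an open discussion an event can move from a counted category to an uncounted one, and nothing in the text preserves the earlier view.

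At stake is whether the halting count, and the summaries of vaccine-related reactions, can be shown to be independent of a party with an interest in the product.

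**Working it through.** **Step 1: what can be reproduced.** The protocol states no error rate or operating characteristic for the halting rule, and section 6.10.2 bases the 36 participants on the regulator's approval, so there is no calculation to reproduce. The group sizes agree: 12 + 12 + 6 + 6 = 36. The rule applies to 12 participants at 2 mg, and to 12 + 6 = 18 at 4 mg if the high-dose and DNA-only groups are counted together.

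**Step 2: the boundary.** With exactly three counted events, one move to possibly or definitely unrelated gives 3 − 1 = 2, and halt becomes continue. With four or more, one such move changes nothing. With two or fewer there is no halt to reverse. The one-event reversal therefore exists only at a count of exactly three.

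**Step 3: how often a halt would rest on exactly three events.** The protocol gives no expected rate of related grade 3 or higher events. I assume a true rate p per participant at one review, at most one event per participant, and independence, so that X ~ Binomial(n, p). Then

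- P(halt) = P(X ≥ 3)
- P(X = 3) = C(n, 3) p³ (1 − p)ⁿ⁻³
- share resting on one event = P(X = 3) / P(X ≥ 3)

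Example, n = 12 and p = 0.10: C(12, 3) = 220, so P(X = 3) = 220 × 0.001 × 0.9⁹ = 0.085. P(X ≥ 3) = 0.111. Share = 0.085 / 0.111 = 77%.

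| n | Assumed p | P(X ≥ 3) | P(X = 3) | Share of halts at exactly three |
|---|---|---|---|---|
| 12 | 5% | 0.020 | 0.017 | 89% |
| 12 | 10% | 0.111 | 0.085 | 77% |
| 12 | 20% | 0.442 | 0.236 | 53% |
| 12 | 30% | 0.747 | 0.240 | 32% |
| 18 | 5% | 0.058 | 0.047 | 81% |
| 18 | 10% | 0.266 | 0.168 | 63% |
| 18 | 20% | 0.729 | 0.230 | 32% |
| 18 | 30% | 0.940 | 0.105 | 11% |

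Where a halt is rare it usually rests on one event. Where it is likely, it depends less on any single one.

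**Step 4: proportional reclassification.** Suppose instead that each related event has probability d of being moved to an unrelated category, so that X ~ Binomial(12, p(1 − d)). The values of d are also assumptions.

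| Assumed p | d = 0 | d = 10% | d = 20% | d = 33% |
|---|---|---|---|---|
| 5% | 2.0% | 1.5% | 1.1% | 0.7% |
| 10% | 11% | 9% | 7% | 4% |
| 20% | 44% | 37% | 30% | 21% |
| 30% | 75% | 67% | 58% | 45% |

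The absolute effect is small at low rates and material at 20% or more. For scale, the Synopsis reports no related grade 3 or higher events in the 12 Phase Ia participants. The one-sided 95% upper bound is 1 − 0.05^(1/12) = 22%. That was rTV alone, so it does not settle the rate after DNA vaccination.

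**Step 5: timing of independent input.** The low-dose review falls within two weeks of each DNA dose, and doses are four weeks apart. A board that meets every two months may next meet after the following dose. Its stated guidance on causality is for serious events, whereas a non-serious grade 3 event also counts toward the halt.

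**The case against.** The plan already has real safeguards.

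- Table 9 gives written criteria, an undeterminable relationship counts as related, and the determination must be confirmed in writing.
- Severity is settled at the site, so the sponsor has no stated hand in whether an event is grade 3.
- Section 6.10.4 keeps the blind through the DNA doses, when the counts in section 6.4.2 are made. In the second enrolment stage both arms receive 4 mg DNA. Unblinding after rTV therefore bears only on section 6.7.2, which applies after every vaccination.
- Discussion can move an event into the count as well as out of it, and any fixed threshold is sensitive to one event, whoever assesses it.

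All of this stands, and it rules out several stronger readings that a reader might infer:

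- *That the sponsor can overrule the site.* Section 6.5.6 describes discussion with written confirmation and gives neither party an override.
- *That the board has no part in causality.* Section 7.3.1 gives it a guiding role for serious events, and it receives regular data reports.
- *That every primary safety endpoint depends on the label.* Table 3 lists grade 3 or higher adverse events without a relatedness condition. Section 6.2.1.1 speaks of reactions, so only part of the endpoint material is exposed.
- *That individual discontinuation rests wholly on the label.* The triggers for symptoms within two hours in sections 6.5.8 and 6.7.1 carry no relatedness condition.

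The safeguards still leave a gap. Counting the undeterminable category helps only while an event stays in it. In Table 9 both that category and possibly unrelated allow for another cause, so the line between them is a judgement. No safeguard says which assessment feeds the count when site and sponsor differ.

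**Conclusion.** The concern holds in limited form. The protocol makes the site's causality assessment provisional, settles it in a discussion that includes the sponsors, and gives no rule for disagreement, while the halting count depends on the result. The documents show that the process permits an event to leave the count this way. They do not show that it favours doing so or that anyone would misuse it.

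The consequence is sharpest at a count of exactly three. In the low-dose group, at assumed rates from 5% to 30%, between 89% and 32% of would-be halts sit there. At the low end the chance of any halt is itself only 2% to 11%, so the absolute effect is small. At 20% or more it is material. These figures rest on assumed rates, independence and at most one event per participant. The protocol counts events, so one participant could contribute several.

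This should be changed: it is a gap in procedure rather than an error in the threshold, and it is cheap to close before data accrue.

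**What to change.** In section 6.5.6:

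1. Record the site's initial causality assessment and the joint determination as separate fields, and keep both.
2. For the halting count and the summaries of vaccine-related events, treat an event as related if either assessment says so.
3. Report the same summaries by the joint determination alone, as a sensitivity summary.
4. Include both assessments in the data reports that the monitoring board already receives.

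Sections 6.4.2 and 6.7.2 should refer to this definition. The thresholds and the clinical stopping rules stay as they are.

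The cost is a short addition to the text, one more case report form field and one more column in the board's reports. The downside is that the related-event count may be somewhat higher than under the joint determination alone, which makes a halt somewhat more likely and shifts the related-event summaries upward. The sensitivity summary shows by how much.
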